## Abstract

The use of high-frequency Transcranial Magnetic Stimulation (HF-rTMS) of the right dorsolateral prefrontal cortex (DLPFC) in treating Post-traumatic Stress Disorder (PTSD) is currently regarded as a level B intervention (probable effectiveness). HF-rTMS has attracted interest as a neuromodulation therapeutic method for PTSD. Prolonged exposure and reactivation therapy are also regarded as first-line treatments for PTSD. Randomized controlled clinical studies examining the effectiveness of several HF-rTMS sessions coupled with psychotherapy have not yet been completed. In total, 102 patients with refractory PTSD will be randomly assigned (1:1) to reactivation therapy, in addition to either active HF-rTMS (20 Hz) or sham HF-rTMS, for 12 sessions in a nationwide, multicenter, double-blind controlled trial. The impact on PTSD symptoms and neurocognitive functioning will be assessed. The primary outcome is the PTSD severity score measured based on the Clinician-Administered PTSD Scale (CAPS-5) at one month. If this additional therapy is successful, it may strengthen the case for regulatory authorities to approve this additional technique of treating PTSD. Additionally, it expands the field of neurostimulation-assisted psychotherapy.

## 1. Background

Post-traumatic stress disorder (PTSD) is defined as a set of symptoms that occur after being exposed to a traumatic incident (re-experiencing the event, avoidance, negative thoughts or sensations, trauma-related arousal, and reactivity). PTSD is ranked as one of the top ten public health issues by the World Health Organization (WHO) [1]. In France in 2014, its frequency was predicted to be 2.4% among civilians [2]. PTSD is frequently a chronic disorder, with just one-third of patients healing after a one-year follow-up and one-third still experiencing symptoms 10 years later [3]. PTSD is associated with significant disability, medical illness, and premature death. The National Comorbidity Survey [3] reports that 16% of PTSD patients have one coexisting psychiatric disorder, 17% have two, and 50% have three or more. Depressive disorders, anxiety disorders, and substance abuse disorders are two to four times more prevalent among individuals with PTSD. Approved therapies are effective in only 41% of patients, even when combined with specific psychotherapy, and the optimal treatment alternatives for non-responding PTSD patients remain unknown. The current mainstay of treatment relies on trauma-focused psychological interventions and psychopharmacological treatments. For most adults newly diagnosed with PTSD, the first-line treatment is trauma-focused psychotherapy that includes exposure, rather than treatment with a serotonergic agent. However, in many cases, a serotonin reuptake inhibitor (SSRI) is a reasonable alternative for patients who prefer medication to psychotherapy or when cognitive-behavioral therapy is unavailable (a frequent situation). Multiple randomized clinical trials [4] have found that patients with PTSD experience reduced symptoms when treated with an SRI compared to a placebo. The majority of PTSD patients receive pharmacological treatment, with antidepressant agents prescribed in 89% of pharmacological treatment cases [5]. Sertraline and paroxetine are the two approved medications [5] and are considered first-line medication treatments for PTSD. However, 41% of subjects fail to respond to antidepressants.

Traumatic reactivation therapy is effective, but remission is achieved in only 40% of subjects [6]. Much of PTSD’s pathophysiology remains unclear. It encompasses a wide range of neurobiological changes, involving disturbances in the hypothalamic–pituitary adrenal axis, hyperactivation of the amygdala complex, and attenuation of some hippocampal and cortical functions (prefrontal cortex) [7]. Abnormalities in these interconnected regions mediate the acquisition of fear responses in PTSD, avoidance of trauma reminders, impaired emotion regulation (manifested as irritability, anger, or reckless behavior), and the persistence of defensive responses once safety has been restored [5]. Functionally, the metabolic activity of the prefrontal–amygdala cortex circuit in PTSD is significantly altered, with increased activation of the amygdala and decreased activation of the prefrontal cortex [7]. An increasing number of studies investigate innovative therapies targeting brain activity to alleviate PTSD symptoms. A treatment augmenting the activity of prefrontal regions could effectively improve executive control of fear responses, thus improving PTSD. Transcranial magnetic stimulation is a noninvasive brain stimulation procedure that can modulate neuronal activity via the administration of magnetic pulses to specific brain areas.

Preliminary studies suggest that transcranial magnetic stimulation of the right dorsolateral prefrontal cortex has a positive effect [5]. Repetitive Transcranial Magnetic Stimulation (rTMS) provides focused, non-invasive stimulation of cortical areas of the central nervous system through an electromagnetic coil placed in contact with the scalp and connected to a magnetic stimulator that discharges short alternating electrical pulses to the central nervous system. The rTMS can be divided into high-frequency (HF) (5–20 Hz) stimulation, which increases cortical excitability, and low-frequency (LF) (≤1 Hz) stimulation, which suppresses excitability. Moreover, repeated sessions at regular intervals help maintain the effect over time [8], and the FDA has approved rTMS for depression and auditory-verbal hallucination treatment.

Although evidence is limited, HF rTMS may improve PTSD symptoms by modulating the prefrontal cortex activity. The mechanisms by which rTMS might exert its effects to mediate symptom improvement in PTSD remain unclear. The most recent meta-analysis [9] on PTSD selected 18 articles for the systematic review, and 11 were suitable for the meta-analysis. The study aimed to determine the most effective stimulation frequency for PTSD symptoms (assessed with CAPS-5). Unilateral high-frequency rTMS stimulation over the DLPFC was mainly performed on the right side.

The combined sample consisted of 377 subjects (217 in active rTMS groups, and 160 in sham-controlled groups). The total number of female participants was 195. The rTMS was an augmentative treatment, i.e., a previously used drug and/or psychological intervention. The authors conclude that additional research is needed, but both HF and LF rTMS can alleviate PTSD symptoms. HF rTMS could improve the primary and related symptoms of PTSD. HF rTMS demonstrated an improvement in the PTSD total score: pooled SMD (pre-post treatment), 3.24; 95% CI 2.24–4.25 (Yan et al.). The dorsolateral prefrontal cortex (DLPFC) and the dorsomedial prefrontal cortex were the most promising sites of stimulation [9]. Four of the studies (all with rTMS HF) reported that the treatment effect of rTMS was preserved for 14 days to 3 months [10,11,12,13]. Focusing on HF studies [10,11,12,13,14], the total number of pulses for the cure ranged from 4000 [11] to 20,160 [12], with an average of 11,520 pulses. We believe that this figure is too low and justifies conducting a study with more pulses per patient.

Furthermore, two trials [12,15] combined rTMS with trauma-focused psychotherapy (the subject recalls their traumatic event) to determine if the combination has an additive effect. Only Isserles et al. (included in the meta-analysis) used recall cues concurrently with stimulation. The primary outcome measure was the CAPS, measured after four treatment weeks. Mean CAPS scores improved from 88 (±5.5) at baseline to 61 (±8.8) in the EXP-STIM group (N = 9), from 86 (±5.4) to 76 (±10.9) in the NOEXP-STIM group (N = 8), and from 86 (±9.2) to 76 (±10.7) in the EXP-SHAM group (N = 9). Significant improvement was demonstrated in the intrusive component of the CAPS scale in patients administered rTMS after exposure to the traumatic event script. The limited number of subjects encouraged the execution of a larger study on a more homogeneous population (resistant PTSD, for example). The study by Kozel et al. is the largest study to date, with 103 veterans randomized to either 9 active (*n* = 54) or sham (*n* = 49) low-frequency (LF) rTMS sessions (1/week) associated with CPT [15]. The rTMS combined with the CPT group showed greater symptom reductions from baseline on CAPS-5 across CPT sessions (t(df ≥ 327) ≤ −2.01 *p* = 0.023, one-tailed). It was a predominantly military population with different traumas from civilian injuries (sexual assault or serious accidents). LF rTMS sessions were performed before psychotherapy.

The rTMS has shown promise as a potential treatment for PTSD, with some studies suggesting that high-frequency stimulation may improve symptoms by modulating prefrontal cortex activity. However, further research is needed to determine the optimal stimulation parameters and patient populations for this intervention. Additionally, more extensive trials exploring the combination of rTMS with trauma-focused psychotherapy may help elucidate whether these treatments have additive effects on PTSD symptom improvement. Considering Yan’s meta-analysis and Kozel’s results, the heterogeneity in rTMS protocols and the limited number of rTMS studies combining cue exposure make it difficult to draw conclusions about the role of rTMS in PTSD. There is a need for intensive clinical trials in this area. We hypothesize greater efficacy of high-frequency (HF) rTMS compared to low-frequency (LF) rTMS [9], as well as improved synergistic action when rTMS and exposure therapy are performed simultaneously, potentially inhibiting the hyperactive amygdala.

The present study protocol aims to elucidate the effect of multiple sessions of HF-rTMS on PTSD symptoms, cognition, and brain functioning. We will conduct a multicenter, double-blind, randomized controlled trial with 102 PTSD patients randomized (1:1) to either 10 sessions of active HF-rTMS + reactivation therapy or 10 sessions of sham HF-rTMS + reactivation therapy. We will investigate the effect of active versus sham HF-rTMS treatment on measures of symptoms and cognition. We expect reduced symptomatology and improved functioning of neurocognitive tasks in the active HF-rTMS-treated group compared to the sham HF-rTMS-treated group. Our protocol proposes a larger number of pulses than the existing literature. We will evaluate the efficacy of combining neuromodulation through rTMS with script-driven imagery in civilian patients who respond insufficiently to first-line treatments with antidepressants.

## 2. Study Aims

We aim to assess the efficacy of high-frequency (HF) rTMS stimulation over the right dorsolateral prefrontal cortex (DLPFC) in patients with PTSD resistant to a first pharmacological line of treatment. The rationale for focusing on this subgroup of patients is twofold: (1) there is a critical need for alternative treatment options for PTSD patients who do not respond to antidepressants, and (2) in these individuals, combining rTMS with reactivation of traumatic memory may be particularly effective by targeting both the prefrontal cortex (activated by rTMS) and the amygdala (reactivated by script-driven imagery). Our study offers another urgently needed treatment option for PTSD patients who are non-responsive to antidepressants. This is the first clinical research study to combine HF rTMS with memory reactivation in a civilian PTSD population resistant to a first-line of a pharmacological agent.

Pairing rTMS with trauma-relevant cues may represent a novel approach to treating PTSD patients. HF-rTMS over the dorsolateral prefrontal cortex (DLPFC) could correct the deficient cortical activation observed in some treatment-resistant PTSD patients. The efficacy of HF-rTMS treatment may be enhanced by combining it with trauma cue exposure (neuro-enhanced psychotherapy), which would engage the prefrontal cortex during sessions. Restoring the activity of prefrontal regions could effectively enhance the executive control of fear responses, thus improving PTSD symptoms. Therefore, this study aims to investigate the efficacy and underlying mechanisms of 10 add-on HF-rTMS sessions as part of a reactivation therapy protocol for PTSD patients resistant to 6 weeks of first-line conventional treatment.

## 3. Primary Research Objective

The primary objective of this study is to evaluate the efficacy of brain modulation by rTMS, combined with simultaneous traumatic memory reactivation, in patients presenting PTSD resistant to one pharmacological agent compared to sham rTMS, with simultaneous traumatic memory reactivation at one month (M1) after the last rTMS session (V13).

## 4. Secondary Research Objective

The secondary objectives of this study are to assess the efficacy of brain modulation via 20 Hz rTMS targeting the right dorsolateral prefrontal cortex, in conjunction with simultaneous traumatic memory reactivation, on the following aspects:Different dimensions of PTSD assessed using CAPS-5 at M3 and M6 post-treatment;The severity of PTSD assessed using PCL at each visit;Anxiety symptoms at V13 (end of treatment), M1, M3, and M6 post-treatment;Depressive symptoms at V13 (end of treatment), M1, M3, and M6 post-treatment;Changes in social cognition at M3 post-treatment;Changes in quality of life at M1, M3, and M6 post-treatment;The safety of the intervention.

## 5. Methods and Design

### 5.1. Study Design

The TRAUMASTIM study is designed as a national multicenter randomized, double-blinded, shamed controlled trial comparing two parallel arms (1:1): rTMS with simultaneous reactivation of traumatic memory in resistant PTSD versus sham rTMS and simultaneous reactivation of traumatic memory.

### 5.2. Ethical Considerations

This study will be approved by the Medical Ethical Committee (IDRCB No 2021-A02532-39-B). Written informed consent will be obtained before screening for inclusion and exclusion criteria takes place.

### 5.3. Inclusion Criteria Patients Aged between 18 and 65 Years

Presenting PTSD according to DSM-5 criteria;Patient with persistent symptoms (PCL > 44) after 6 weeks of treatment with SSRI;Patient with health insurance (AME excepted);Signed written informed consent.

#### Exclusion Criteria History of Epilepsy or Seizure

Cochlear implants;Cardiac pacemaker or intracardiac lines, or metal in the body;Strong dissociative tendencies, evidenced by an average score > 20 on the DES;Lifetime psychotic or bipolar disorder;Antisocial personality or borderline personality;Brain injury defined by medical report;Current substance dependence (including alcohol, excluding tobacco);Acute suicidal ideation;No adequate mastering of the French language or no ability to consent;Pregnancy (confirmed by a urine beta-HCG) or breastfeeding;Absence of birth control;Patient under legal protection measures and/or deprived of freedom;Participation in any other interventional study or in the exclusion period of any other interventional study.

### 5.4. Intervention

#### 5.4.1. rTMS Protocol

The intervention consists of 12 HF-rTMS sessions in the right DLPFC (rDLPFC) on 12 workdays. The HF-rTMS parameters of the active intervention are as follows: active high-frequency 20 Hz, 3 to 4 sessions of 10 min per week, 2000 pulses/session, and a motor threshold of 110%. In our centers, we regularly offer 3 to 4 rTMS sessions per week for patients with depression, which has proven to be both feasible in terms of logistics and well accepted by the patients receiving the treatment. The number of sessions per week will be determined based on the logistical constraints of the investigating centers and the patients being stimulated. The device used will be an electromagnetic stimulator, which is used to artificially provoke a functional activity (GMDN 13762) CE marked, Class IIa.

The rDLPFC will be located at position F4 using the International 10–20 EEG system or a neuronavigation system. During the stimulation, participants will be seated on a comfortable chair with extra neck support. One stimulation session will take approximately 10 min.

The motor threshold will be determined at rest before the first stimulation session, using single-pulse TMS in combination with motor-evoked potentials. The optimal spot on the scalp for stimulation of the right abductor pollicis brevis muscle will be located, and the motor threshold will be established by delivering single stimulations to the motor cortex. The motor threshold, defined as the lowest stimulation intensity producing five motor evoked potentials (MEPs) of at least 50 μV in 5 out of 10 stimulations, will be measured by gradually increasing the stimulation intensity. The intervention will be applied by an rTMS-trained researcher.

Sham rTMS will be delivered, following the same procedure. The trauma memory reactivation procedure will be the same as that in the experimental group. Sham rTMS will be performed with a special probe for sham procedures. The instruction to use sham rTMS will be the same as that for the active device. A sham coil providing the same noise, heat, clicks, and sensations as the active coil will be used without any magnetic pulse.

#### 5.4.2. Reactivation Therapy

The reactivation therapy consists of the development of a traumatic script where participants will describe their traumatic event during a “script” preparation session, which will be used to reactivate the traumatic memory before each rTMS session. The intervention will be performed by a reactivation therapy-trained physician.

### 5.5. Number of Participating Sites

There will be 8 national sites involved, located in hospitals (outpatient or inpatient settings).

### 5.6. Participant Identification

Participants in this clinical investigation will be identified using the following format: site number (3 digits); sequential enrollment number for the site (4 digits); surname initial and first name initial. This unique reference number will be used throughout the duration of the clinical investigation. A randomization number will also be assigned when the participant is randomized, following the RXXX format, in accordance with the sponsor’s procedures.

### 5.7. Randomization

A computer-generated randomization list (allocation ratio: 1:1) will be created by the Unité de Recherche Clinique (URC) of Saint-Antoine Hospital (AP-HP). Randomization will be block-balanced and stratified by site, with block widths undisclosed to investigators. The rTMS operator will perform randomization through a web interface (CleanWeb Software, Telemedicine, Paris, France) during the inclusion visit or before the first rTMS session.

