## 6. Procedure and Data Collection

### 6.1. Inclusion Procedure

Patients will be recruited during an appointment at a participating specialized trauma unit (trauma center). Patients may be either hospitalized or treated as outpatients. During the selection visit and prior to any research-related examination, the physician will propose the study to the patient, informing them about the objective, the nature of the constraints, the computerized processing of the data that will be collected during this research, and their rights of access, opposition, and rectification to these data. During this visit, the eligibility criteria will be verified by the investigator or co-investigator. An information form summarizing these points will be provided to the patient. If they are interested, informed consent will be signed, and the participant will be screened for inclusion and exclusion criteria. If a patient meets all the inclusion criteria and none of the exclusion criteria, they will be included in the study by the researcher.

A computer-generated randomization list (1:1) will be created by the Clinical Research Unit (URC) of Saint-Antoine Hospital (AP-HP). Randomization will be block-balanced and stratified on-site. The width of the blocks will not be disclosed to investigators. Randomization will be performed using a web interface (CleanWeb 2.0 Software, Telemedicine, Paris, France) at the inclusion visit or before the first rTMS session by the rTMS operator. The allocated arm (active or sham rTMS) will not be included in the medical records. The blinding of the allocated treatment will be applied to both the included patients and investigators involved in the patient’s inclusion and follow-up. The operator performing the rTMS will be the only one aware of the sham or active condition. This operator will not be involved in the patient’s follow-up and evaluation.

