### 8.2. Primary Criterion Analysis

An analysis will be conducted based on the intent-to-treat (ITT) population.

The CAPS total severity score at M1 will be compared between groups using the Student *t*-test. In the case of a non-normal distribution, transformation will be performed. Sensitivity analyses on available data and on per protocol population using the same methods will be performed.

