## Figures and Tables

**Figure 1 brainsci-13-01274-f001:**
[figure not shown]
Overview of the intervention.

**Table 1 brainsci-13-01274-t001:** Overview of instruments and assessment.

Visit	0	1	2	3	4	5	6	7	8	9	10	11	12	13	14	**15**	**16**
PDI	✕																
HCG		✕															
Active/Sham rTMS			✕	✕	✕	✕	✕	✕	✕	✕	✕	✕	✕	✕			
Trauma Script		✕															
Reactivation			✕	✕	✕	✕	✕	✕	✕	✕	✕	✕	✕	✕			
MINI-5		✕													✕		
CAPS-5	✕														✕	✕	✕
PCL-5	✕		✕			✕			✕			✕		✕	✕	✕	✕
CGI			✕			✕			✕			✕		✕	✕	✕	✕
Eckman Test		✕														✕	
Empathy Quotient		✕														✕	
Baron-Cohen		✕														✕	
TAS-20		✕														✕	
HAM-D		✕												✕	✕	✕	✕
HAM-A		✕												✕	✕	✕	✕
WHOQOL		✕													✕	✕	✕
EQ-5D-5L		✕													✕	✕	✕

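### Randomisation may take place at the inclusion visit, before the V2 start of stimulation; tying it to V2 would avoid a small, unquantified loss of power

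*Protocol article*

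**What the plan says.** Section 5.7 allows randomisation "during the inclusion visit or before the first rTMS session". Section 6.1 gives the same two options: "at the inclusion visit or before the first rTMS session by the rTMS operator". Neither section says which applies when, or how long before the first session randomisation may take place.

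Table 1 ("Overview of instruments and assessment") shows this order of visits:
- **V0:** CAPS-5 and PCL-5.
- **V1:** urine HCG, MINI, trauma script, HAM-D, HAM-A, social cognition and quality of life.
- **V2:** first active or sham stimulation, with the first reactivation.

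The article does not state whether the inclusion visit is V0 or V1, and it gives no interval between V1 and V2.

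On eligibility, section 6.1 says of the selection visit: "During this visit, the eligibility criteria will be verified by the investigator or co-investigator". It adds: "If a patient meets all the inclusion criteria and none of the exclusion criteria, they will be included in the study by the researcher".

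On the primary analysis, section 8.2 says: "An analysis will be conducted based on the intent-to-treat (ITT) population". It continues: "Sensitivity analyses on available data and on per protocol population using the same methods will be performed". Section 8.1 asks for 92 patients and raises this to 102 to allow for 10% non-evaluable.

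**The concern.** Whether the inclusion visit is V0 or V1, it comes before V2. The earlier option therefore opens a gap between allocation and the start of treatment. In this trial the gap can include an event that may prompt withdrawal: at V1, patients whose disorder has avoidance as a core feature are asked to describe their traumatic event for the script (section 5.4.2). Someone who does not return for V2 has already been randomised and belongs to the ITT set without having received a single session.

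Such a patient carries no information about stimulation. If an M1 score is obtained or filled in, the expected difference between arms shrinks. If there is no M1 score, part of the 10% allowance is used up, and that allowance must also cover every loss between V2 and M1. Once patients have been randomised early, the loss cannot be undone without departing from ITT. The later option avoids nearly all of it.

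**Working it through.** **Inputs.** From section 8.1: difference 15 points, SD 24 in both arms (the article calls it a standard error), two-sided alpha 5%, power 85%, 92 evaluable patients, 10% non-evaluable, 102 randomised. From section 5.7: allocation 1:1. The share *f* of each arm that is randomised but never stimulated is not in the article, so it is an assumption, varied below from 0% to 10%.

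**1. Reproduce the plan's figures.** With the normal approximation, n per arm = 2 × (1.960 + 1.036)² × 24² / 15² = 45.97, rounded up to 46, so 92 in total. This agrees with the article. The exact t calculation gives 47 per arm (94), which is close. For the allowance, 92 / 0.9 = 102.2 and 92 × 1.1 = 101.2, both consistent with the stated 102.

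**2. Case A: never-stimulated patients have an M1 score, observed or imputed.** Assume they have the sham-arm mean. Then:
- Expected difference = 15 × (1 − f), a loss of 0.15 points for each 1%.
- Active-arm variance = 24² + f(1 − f) × 15², because that arm is now a mixture.
- Pooled SD = the square root of the mean of 24² and that variance.
- Power comes from the noncentral t distribution with noncentrality = difference / (SD × √(2/n)).

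Example at f = 5%: difference 14.25; active-arm variance 576 + 0.0475 × 225 = 586.7; pooled SD √((576 + 586.7)/2) = 24.11.

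| f | Difference | Pooled SD | Power, 51 per arm | Power, 46 per arm |
|---|---|---|---|---|
| 0% | 15.00 | 24.00 | 87.8% | 84.3% |
| 2% | 14.70 | 24.05 | 86.4% | 82.7% |
| 5% | 14.25 | 24.11 | 84.0% | 80.1% |
| 10% | 13.50 | 24.21 | 79.6% | 75.4% |

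With all 102 analysed, power falls below the planned 85% at f of about 3.8% (0.038 × 51 = 1.9, roughly two patients per arm) and below 80% at about 9.6%. The 46-per-arm column assumes that the whole 10% allowance has already gone on other losses, so it is the harsher case.

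**3. Case B: never-stimulated patients have no M1 score and leave the comparison.** The 15-point difference is not diluted; only the numbers fall. Starting from 51 per arm and rounding down, a 5% loss leaves 48 per arm and power 85.8%, and a 10% loss leaves 45 per arm and 83.5%. That is roughly what the 10% allowance was meant to absorb, but nothing then remains for losses after V2.

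**4. Later option only.** With randomisation immediately before the V2 session, f from this source is close to zero and the planned figures stand.

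**The case against.** Flexible timing is a legitimate operational choice, and much can be said for leaving it alone.

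- **No rate, no interval.** The article gives neither a pre-treatment withdrawal rate nor the time from V1 to V2, so the power figures illustrate an assumption. This stands.
- **Dilution is conditional.** Someone who withdraws before V2 may well have no M1 score, and then the 10% allowance applies. This stands, with one qualification. Section 8.2 makes the available-data analysis a sensitivity analysis, which suggests that the primary analysis is meant to retain patients without data. How it would do so may be set out in an analysis plan not shown here.
- **Failed eligibility checks.** Because HCG and MINI are at V1, and one exclusion reads "Pregnancy (confirmed by a urine beta-HCG) or breastfeeding", a reader might infer that patients are randomised and then found ineligible. The article does not support this. Section 6.1 requires every criterion to be met before inclusion, and the natural mapping is V0 for selection and V1 for inclusion. The problem would arise only if inclusion were V0, which the article does not say.
- **Baseline ratings after allocation.** A reader might also worry that V1 ratings are recorded after randomisation. Patients and assessing investigators are blinded and the operator takes no part in evaluation (section 5.8). The baseline CAPS-5 is at V0, and the primary test uses only M1 scores. The risk is low.
- **Retention is what ITT means.** This is correct. The aim is to have fewer such patients, not to exclude them.

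What remains after these points is withdrawal in the gap, which can occur whether inclusion is V0 or V1.

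**Conclusion.** The point holds as a minor matter of efficiency. The plan permits allocation at least one visit before treatment can start, and patients lost in that gap cost power either through dilution or through the non-evaluable allowance. The size is unknown. With all 102 analysed and such patients scored at M1 like the sham arm, power would go from 87.8% with none to 84.0% at 5% and 79.6% at 10%. Up to about 3.8% is absorbed before power drops below 85%.

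It would be wrong to read this as a bias in favour of active stimulation. Because patients are blinded, withdrawal before V2 should not depend on arm, so the estimate would be conservative. Nor is it an error in the sample size, which reproduces.

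**What to change.** In sections 5.7 and 6.1, delete the inclusion-visit option. State that randomisation takes place as shortly as practicable ahead of the first stimulation at V2, and only after all eligibility checks (HCG and MINI included), all V0 and V1 baseline assessments and the trauma script are complete.

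The cost is one sentence in each section. No visit or patient is added, and the later time is already permitted. The one practical demand is on the allocation relay in section 5.8: the two independent staff members must receive the randomisation email and pass it to the operator on or just before the day of V2. Sites should confirm that this works without delaying sessions.
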